#### *Storage and analysis of* Cytosponge™ *samples*

Cytosponge™ samples will be sent directly from GP sites to Cambridge University Hospitals NHS Foundation Trust Research Tissue Bank (CUHTB) to be processed into Formalin Fixed Paraffin Embedded (FFPE) blocks for TFF3 testing, and H&E analysis as described previously for the BEST2 trial [14].

#### Cytosponge™-TFF3 results

Patients will be informed about their Cytosponge™-TFF3 results by a standardised Cytosponge™ feedback letter from their GP within four to 6 weeks. Where the test is a low-confidence negative result, i.e. the sample fails in processing or is equivocal, the patient may be invited for a repeat test at a suitable location depending on local capacity. Other benign conditions of the oesophagus will be reported with the TFF3 result.

### Endoscopies

#### Invitation for endoscopies - intervention arm: TFF3-positive patients

Patients with a positive TFF3 test will be contacted by their GP to inform them of the result and offer an endoscopy examination to confirm the diagnosis. If this is agreed by the patient the GP informs the research nurse to arrange the procedure at the local endoscopy unit.

#### Invitation for research endoscopies - 10% of patients who do not require diagnostic endoscopy (all arms)

10% of the total number of study participants who have not had an endoscopy during the study will be invited for a research endoscopy at 12 months after entry into the study, including participants who have declined the original Cytosponge™-TFF3 intervention. Since BEST3 will be assessing the acceptability of endoscopy compared with Cytosponge™-TFF3, the intervention here will be “invitation to endoscopy”. Participants to be invited will be selected at random using the random selection function in practice databases. They will receive an invitation letter for a research endoscopy at their local hospital-based endoscopy clinic including an endoscopy-specific BEST3 Patient Information Sheet and a consent form.

#### Endoscopy procedures

Standard trans-oral endoscopy following BSG guidelines [21] for diagnosis of BE will be carried out. During the procedure the endoscopist will note the diagnostic endoscopic landmarks for BE using a standard protocol and in line with the Seattle protocol [22]:For all endoscopies where BE is found, biopsies will be collected (in all 4 quadrants) every 2 cm according to surveillance guidelines. In addition, endoscopically-suspicious areas will be targeted for biopsies.A further two biopsies from the gastro-oesophageal junction (GOJ) will be collected (below the z-line) for research purposes from both BE positive and patients with a TFF3 negative test.All biopsy samples will be processed and analysed by the local pathologist according to standard clinical practice including for benign conditions.Study participants will be informed about endoscopy findings in the usual way via a letter from the gastroenterologist copied to their GP.Endoscopic images will be requested of every GOJ and newly diagnosed BE to try to exclude misdiagnosed hiatus hernias and intestinal metaplasia (IM) at normal appearing GOJ.

#### Diagnosis of BE

Diagnosis of BE as the primary endpoint will be defined at three different levels of certainty:Diagnosis by the endoscopist or gastroenterologist following BSG guidelines∘ > 3 cm likely correct;∘ < 3 cm more suspect unless biopsy with IM;Confirmed by study pathologist or gastroenterologist∘ >C1 or >M3 +IM on biopsy;IM on biopsy∘ any length.

As a secondary endpoint we will also use a scoring system for BE according to severity (Table 5).

**Table 5 Tab5:** Proposed BE scoring system

Score	BE severity
0	Pathology report not available
1	Intestinal metaplasia (IM) on biopsy and endoscopic findings not seen in categories below
2	C1 or C0 M3 + IM
3	C2 or more, C0 M4 or more +IM
4	C3 or more
5	Low grade dysplasia (LGD)
6	High grade dysplasia (HGD) or T1a cancer

TFF3 positive patients will also be asked to provide a saliva sample using the Oragene DNA kit at their endoscopy appointment. These samples will be stored for future genetic research.

### Acceptability measures- intervention group only

#### Patient acceptability measures

##### Baseline

Participants receiving the Cytosponge™-TFF3 test will be asked to complete a baseline questionnaire consisting of:I.STAI-6, a short-form of the state scale of the Spielberger State-Trait Anxiety Inventory (STAI); this 6-item self-completed scale has been widely used to measure short-lived anxiety in relation to health experiences [23]. To aid the appointment process, and to ensure that the state being measured accurately reflects views about the procedure, the questionnaire will be provided to the patient prior to consent in the clinic waiting room area. If the patient does not go on to consent into the study, their questionnaire response will be disposed of securely.

Once consent has been obtained:II.Lifestyle and family history questionnaire, covering education, history of smoking and alcohol, and any family history of heartburn, BE, oesophageal cancer and any other type of cancer.III.Perceived risk of oesophageal cancer, using 2 items which have been widely used for other cancer risk assessments to assess perceived risk of developing EAC and perceived risk compared with a person of the same age (relative risk) [24];

##### 7–14 day follow-up

Seven to fourteen days post-study consultation, all participants receiving the Cytosponge™-TFF3 test will be either sent an email or text message with a link to an online questionnaire (or mailed a questionnaire as preferred). This questionnaire will consist of:I.the Inventory to Assess Patient Satisfaction, used following flexible sigmoidoscopy screening, amended for the Cytosponge™-TFF3 test, and validated using face validation with 8 patients, who were either at high risk of BE or have had the Cytosponge™-TFF3 test; this has a 5 point ordinal scale with 22 items [25];II.a visual analogue scale (VAS) in which 0 represents “Completely unacceptable” and 10 represents “Completely acceptable” [13];III.Perceived risk of oesophageal cancer [24];IV.STAI-6 [23].

If the follow-up questionnaire has not been returned after 2 weeks, a reminder will be sent to participants who have provided an e-mail address.

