**Secondary endpoints (all to be estimated together with (nominal) 95% Confidence Intervals):**
To estimate the diagnostic accuracy of the Cytosponge™ in primary care the sensitivity will be calculated as the proportion of TFF3 positive tests in patients with endoscopy confirmed BE (gold standard). The specificity will be calculated as the proportion of TFF3 negative tests in endoscopy confirmed BE negative patients amongst the 10% participants randomly invited to endoscopy from TFF3 negative patients.To confirm the prevalence and incidence of BE and cancer stage diagnosis in the intervention and control arms for 10 years: Long term follow up data will allow Cox proportional hazard model analysis to compare oesophageal cancer and death rates.The acceptability of both Cytosponge™ and endoscopy tests will be assessed as the proportion of patients willing to have the test among patients offered the test. 95% confidence intervals (Clopper-Pearson) will be used.

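### The reminder for the day 7–14 questionnaire reaches only those who gave an e-mail address, so follow-up effort on the post-test acceptability measures is unequal

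*Protocol article*

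**What the plan says.** The section on 7–14 day follow-up in the protocol article states that "all participants receiving the Cytosponge™-TFF3 test will be either sent an email or text message with a link to an online questionnaire", with a paper alternative: "or mailed a questionnaire as preferred". The questionnaire has four parts: the adapted satisfaction inventory, a 0–10 VAS of acceptability, perceived risk of oesophageal cancer, and STAI-6.

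The same section then sets the one follow-up rule. When the form is still missing two weeks later, "a reminder will be sent to participants who have provided an e-mail address". No text or postal reminder for this questionnaire appears anywhere in the article. The single reminder by post, telephone or text in Table 6 (pilot phase amendments) is a different one. It concerns the invitation to book a test appointment.

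**The concern.** Three delivery routes are offered, but the attempt to recover missing forms depends on one contact detail. Participants without a recorded e-mail address get one chance to respond, and the others get two. If the two groups also answer differently, responders will not represent those tested. An analysis plan can describe or weight for this, but it cannot recover answers that were never sought.

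Table 2 shows what rests on this form:

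- **Test experience:** the VAS and the inventory are its quantitative sources.
- **Willingness to repeat the procedure:** the inventory is its only listed source. The interviews of up to 30 patients are listed for other items.
- **Change in STAI-6 and in perceived risk:** baseline values are collected in clinic, so change is seen only in those who return the follow-up form.

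The trial population is aged 50 and over with no upper limit, and the article presents it as the population in which the test would be used. Responders who resemble those tested are therefore worth having.

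**Working it through.** **1. What depends on the reminder rule.**

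| Measure | Source in the protocol article | Exposed? |
|---|---|---|
| Inventory, VAS, follow-up STAI-6, follow-up perceived risk | 7–14 day follow-up | Yes |
| Acceptability analysis in the secondary endpoints: "will be assessed as the proportion of patients willing to have the test among patients offered the test" | Invitation and consent counts | No |
| Swallowing failures and attempts | Table 2 | No |
| Baseline STAI-6: "the questionnaire will be provided to the patient prior to consent in the clinic waiting room area" | Baseline | No |
| Safety at 7 days | Nurse telephones all tested participants | No |
| BE diagnosis at 12 months (primary) | GP, endoscopy and pathology records | No |

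**2. Figures in the document.** There is no expected questionnaire response, e-mail share or precision target for these measures, so there is no stated figure to reproduce. The number tested is 8488/2 × 0.50 = 2122 under the original design, as stated. Under the amended design it is 15,656/2 × 0.27 = 2113.6, or about 2,114, assuming equal arms.

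**3. Illustration on assumed inputs.** Let e be the share with an e-mail address (50–90%), r the first response, equal in both groups (50–70%), c the share of non-responders whom the reminder converts (10–30%), and d the true difference in mean VAS between the groups (0.5–1.0 points).

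- Response with e-mail = r + (1 − r)c; response without = r; gap = (1 − r)c.
- Smallest gap: 0.30 × 0.10 = 3 points. Largest gap: 0.50 × 0.30 = 15 points. With c = 0 the gap is 0.
- E-mail share among responders, s = e[r + (1 − r)c] / {e[r + (1 − r)c] + (1 − e)r}.
- Shift in mean VAS = (s − e)d.

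For e = 0.5, r = 0.5, c = 0.3: s = 0.325/(0.325 + 0.250) = 0.565. With d = 1.0 the shift is 0.065.

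| e | r | c | Gap (points) | s | Shift, d = 0.5 | Shift, d = 1.0 |
|---|---|---|---|---|---|---|
| 0.5 | 0.5 | 0.3 | 15 | 0.565 | 0.033 | 0.065 |
| 0.5 | 0.5 | 0.1 | 5 | 0.524 | 0.012 | 0.024 |
| 0.7 | 0.5 | 0.3 | 15 | 0.752 | 0.026 | 0.052 |
| 0.7 | 0.7 | 0.1 | 3 | 0.709 | 0.004 | 0.009 |
| 0.9 | 0.5 | 0.3 | 15 | 0.921 | 0.011 | 0.021 |
| 0.9 | 0.7 | 0.1 | 3 | 0.904 | 0.002 | 0.004 |

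Over the whole grid the shift runs from about 0.002 to 0.065 points.

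**4. If first response is not equal.** With 50% (e-mail) and 60% (no e-mail), a 20% yield gives 0.50 + 0.50 × 0.20 = 0.60, and the gap closes to 0. With 60% and 50%, the same yield gives 0.60 + 0.40 × 0.20 = 0.68, and the gap widens from 10 to 18 points. The direction is therefore not fixed.

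**5. Responses forgone.** This is 2,114 × (1 − e) × (1 − r)c. It runs from 2,114 × 0.10 × 0.03 ≈ 6 to 2,114 × 0.50 × 0.15 ≈ 159.

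**The case against.** The strongest case against is that nothing here is an error or a contradiction. It is a detail of reminder logistics for secondary measures in the intervention arm only. Clinic data on tested participants allow responders to be compared with non-responders, interviews are spread across ages, and the handling of missing forms may be set out in an analysis plan that is not shown. All of that stands, and it limits the weight of the point. It does not remove it, because the article states the rule outright and gives no reason for limiting it.

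A reader might go further, and the document does not support these steps:

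- **That text and postal participants are never reminded, or that digital access is the dividing line.** The criterion is a supplied e-mail address. Someone who chose paper but gave an address is reminded. Someone who uses a text link without giving one is online and is not.
- **That responders will be younger, or the results biased.** Neither e-mail share nor response is reported by age. Unequal response biases a mean only if the answers differ too.
- **That these are the trial's only quantitative acceptability outcomes.** Uptake, swallowing failures and baseline scores are quantitative and unaffected.
- **That postage is the only drawback of a wider reminder.** A form sent at day 7–14 and chased two weeks later is chased at about day 21–28. The section on test results allows four to six weeks for the result letter. Slower postal returns may be completed after the result is known, which matters for STAI-6 and perceived risk. E-mail reminders carry some of this risk already.

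**Conclusion.** The point holds as a minor design improvement. As written, follow-up effort is unequal, and response to the four post-test measures can depend on having given an e-mail address. The direction and size of any bias are unknown from the document. If first response is equal at 50–70% and the reminder converts 10–30% of non-responders, the response gap is 3 to 15 percentage points. Adding an e-mail share of 50–90% and a true VAS difference of 0.5–1.0 points, the mean VAS shifts by less than 0.1 point. All these inputs are assumptions. The stronger case for changing the rule is equal effort and additional responses, not correction of a large bias. The trial's main conclusion does not depend on it.

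**What to change.** Send the single two-week reminder to every non-responder by the route used for the questionnaire (e-mail, text or post). Report the response rate by route. Record the completion date of each form relative to the result letter, and take it into account when analysing STAI-6 and perceived risk.

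The cost is small. On the assumed ranges, the extra reminders number 2,114 × (1 − e) × (1 − r). That is from 2,114 × 0.10 × 0.30 ≈ 63 to 2,114 × 0.50 × 0.50 ≈ 529 texts or letters, over routes that already deliver this questionnaire. The other cost is that some postal answers will arrive after the result, which the recorded dates make visible.

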### Intervention acceptability for patients and health care professionals

#### Patients

Some participants from intervention practices will be interviewed to increase understanding of patient views on the Cytosponge™-TFF3 test and its use in the primary care setting. Up to 30 patients across a range of ages and including both men and women, will be interviewed within six to 8 weeks of their trial consultation. Patients will be interviewed in their own home or a place of their choosing. They will provide written consent prior to interviews commencing.

Data will be audio-recorded and transcribed professionally. It will remain confidential and will not be shared with their GP. Data will be analysed using Thematic Analysis [26], supported by NVivo. We expect the following themes to be explored in the analysis: patient views of acceptability of Cytosponge™-TFF3 test use in primary care, and patient understandings and perceptions of ‘risk’ in relation to their symptoms. As qualitative analysis is an inductive and iterative process, further themes will evolve throughout the analytical process.

#### Healthcare professionals

##### GPs

Semi-structured interviews with up to 20 GPs from intervention practices will be undertaken to identify and gain an understanding of the facilitators and constraints influencing use of the Cytosponge™ in primary care routine clinical practice. GPs will be recruited purposively to sample as widely as possible (region, gender, age, trainer status, rural / urban location). GPs can choose to be interviewed face-to-face or by telephone. Those who are interviewed by telephone will be asked to provide verbal consent at the beginning of the interview and also complete a written consent form to be returned by post. Data collection, transcription and analysis will be undertaken in a similar way to the patient interviews.

##### Research nurses

All research nurses involved in delivering the intervention will be asked to complete a short on-line questionnaire at the beginning and end of their involvement in the study. This will focus on issues around their training, patient recruitment to their clinics, and delivering the intervention. We will also undertake semi-structured interviews with up to 20 research nurses from intervention practices, to identify and gain an understanding of the facilitators and constraints influencing use of the Cytosponge™-TFF3 test in primary care routine clinical practice. Research nurses will be recruited to sample as widely as possible (region, gender, age, trainer status, rural / urban location), for a telephone interview. The methods of data collection, transcription and analysis will be identical to the GP interviews. In addition, we will undertake descriptive analyses of the questionnaire data, and use both datasets in a mixed methods analysis to look for overarching themes.

### Involvement of public and patient involvement representatives

The BEST3 study design and key documents (introductory letter, Cytosponge™-TFF3 test leaflet, and PIS) were discussed with a group of seven PPI representatives based at Cambridge University Hospitals NHS Foundation Trust. This group reviewed all patient facing materials. Their advice will be used to further guide any changes to the design of the study and study materials. There are two active lay members of the BEST3 trial steering committee (TSC). As part of the TSC, they are involved in the remainder of the trial, including analysis of results and dissemination of findings.

### Statistics and data analysis

#### Sample size calculations

The sample size calculation is based on the following assumptions:i.BE prevalence in individuals eligible for the study is 4–5%;ii.10% of patients in the usual care arm will be referred to endoscopy for clinical reasons (after excluding urgent referral);iii.The prevalence of BE in patients referred to endoscopy in the usual care arm is 6%;iv.Uptake of the Cytosponge™ test is currently expected to be 50%;v.Cytosponge™-TFF3 sensitivity is 85%  [14];vi.Endoscopy sensitivity is 100%.

The assumed 4% prevalence of BE in individuals eligible for the study was based on the BEST1 trial, which reported 3% in a population, but included patients with less severe GORD compared with the BEST3 trial [13]. Since only 50% of patients in the Cytosponge™ arm are predicted to have the Cytosponge™ test and patients who do not take up the offer of the test will have the same management as if they were in the usual care arm we only expect 2.0% of patients in the intervention arm to be diagnosed with BE. Furthermore, we expect 0.6% of patients in the usual care arm to be diagnosed with BE. For a 90% power (not allowing for clustering) comparing 0.6% with 2.0%, we would need 3028 individuals (1514 in each arm).

To account for the fact that individuals within a cluster, here a GP practice, might be more similar to each other than to individuals in other clusters, the number of participants required for an individually randomized trial has to be increased. The sample size calculations were adjusted for cluster randomization using the variance inflation factor (VIF) [27]. We allowed for variation in practice size and adjusted the sample size calculations for three groups of practices recruiting either 50–60, 61–74 and 75–100 patients. Allowing for intra-cluster correlation of 0.025, an overall coefficient of variation of 0.2, and mean cluster sizes of 55, 68 and 88 the VIF was estimated as 2.4, 2.7 and 3.3 respectively. Multiplying the VIF with the sample size estimated for individual randomization for each stratum, we would need a total of 8488^1^ patients. If we are recruiting three groups of 40 practices with 50–60, 61–74, or 75–100 patients each, then 120 practices will result in approximately 90% power. Assuming 50% uptake, this would result in 2122 patients having the Cytosponge™ test. If the uptake is lower, the overall number of patients entered into BEST3 will be increased so that still a total of 2122 patients will have the Cytosponge test.

### Statistical analysis

#### Primary endpoint

##### Null hypothesis

The BE detection rate at 12 months (excluding any found on random exit endoscopies) is the same in the intervention (Cytosponge™-TFF3 test) arm and the control (usual care) arm.

##### Alternative hypothesis

The BE detection rate at 12 months is not the same in the intervention (Cytosponge™-TFF3 test) arm compared with the control (usual care) arm.

To determine whether the invitation to the Cytosponge™-TFF3 test leads to an increase in the number of patients diagnosed with BE compared with the usual clinical care pathway we will compare BE diagnosis between intervention and the control arms in all patients entered into the study. We shall compare the proportions of BE between the two groups at 12 months after study entry using a generalised estimating equation (GEE) with BE diagnosis as the binary outcome comparing the two arms as fixed effects with adjustment for age, gender, BMI, and length and dose of acid suppressive treatment together with cluster as a random effect. We will use both the assumed intra-class correlation (0.025) and the estimated intra-class correlation. Statistical significance will be based on a two-sided test with alpha equal to 5%.

**Secondary endpoints (all to be estimated together with (nominal) 95% Confidence Intervals):**
To estimate the diagnostic accuracy of the Cytosponge™ in primary care the sensitivity will be calculated as the proportion of TFF3 positive tests in patients with endoscopy confirmed BE (gold standard). The specificity will be calculated as the proportion of TFF3 negative tests in endoscopy confirmed BE negative patients amongst the 10% participants randomly invited to endoscopy from TFF3 negative patients.To confirm the prevalence and incidence of BE and cancer stage diagnosis in the intervention and control arms for 10 years: Long term follow up data will allow Cox proportional hazard model analysis to compare oesophageal cancer and death rates.The acceptability of both Cytosponge™ and endoscopy tests will be assessed as the proportion of patients willing to have the test among patients offered the test. 95% confidence intervals (Clopper-Pearson) will be used.

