To assess the diagnostic accuracy of the Cytosponge™ in primary care	Positive Predictive Value (PPV), Negative Predictive Value (NPV) in relation to the length of BE	N/A	- PPV: proportion of TFF3 positive results confirmed to have BE by endoscopy - NPV: proportion of TFF3 negative cases confirmed to not have BE by endoscopy (10% endoscopy)
To assess diagnostic performance of Cytosponge™ in detecting severity for BE	Score of BE severity based on BE biopsy results	N/A	Endoscopy reports for participants
To report on the sampling adequacy	Inadequacy rate (same as BEST1 and BEST2)	N/A	CRF to capture: - Sample sufficient to generate result - Proportion of Cytosponge™ samples with < 5 and < 1 columnar cells (minimal standard)
To confirm the endoscopy referral rate in the intervention arm	Proportion positive out of all adequate TFF3 tests and out of all patients swallowing a Cytosponge™ at least once	N/A	Cytosponge™-TFF3 test results
To report on patient acceptability for Cytosponge™	(i) Willingness: proportion of patients offered Cytosponge™ test who accept (ii) Cytosponge™ swallowing failures (iii) Increased and decreased cancer worry due to procedure and results (iv) Long term emotional or physical harm caused by procedure (v) Test experience (vi) Willingness to have repeat procedure	N/A	(i) Number of patients invited vs those consenting to Cytosponge™-TFF3 test (ii) Number of patients who fail to swallow and number of attempts Acceptability measures at baseline: (iii) STAI-6 (iv) Perceived risk of oesophageal cancer Acceptability measures at day 7–14: (iii) Perceived risk of oesophageal cancer (iv) STAI-6 (v) A visual analogue scale to rate experience (v-vi) the Inventory to Assess Patient Satisfaction, (iii – v) up to 30 qualitative patient interviews
To assess physician/nurse acceptability of the Cytosponge™	Experience and acceptability of Cytosponge™: administration, skills, reliability, side effects, user information	N/A	Qualitative interviews of clinical staff
To report on the safety of the Cytosponge™ in primary care	Any ADE/ARs reported by patients up to 7 days post swallowing	N/A	Contact card given in case of ADE/SADE and 7-day telephone call

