#### Secondary objectives

The main secondary objectives are to evaluate the cost and cost-effectiveness of the Cytosponge™-TFF3 test versus usual care. Other secondary objectives include confirming the safety and diagnostic accuracy of the Cytosponge™-TFF3 test and determining the uptake in primary care. Inviting 10% of BEST3 participants for a research endoscopy will enable us to assess the diagnostic accuracy of the Cytosponge™-TFF3 test in primary care. We will also assess the acceptability of the Cytosponge™-TFF3 test to patients, GPs and practice nurses, and their experiences of its use in primary care. Long term objectives are to confirm the prevalence and incidence of BE, EAC and cancer of the gastric cardia in a primary care population consulting with reflux predominant symptoms and to undertake modelling to predict the reduction in EAC related mortality from this strategy.

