## Methods

### Design

This is a pragmatic multi-site cluster randomised controlled trial where approximately 120 general practices will be randomised 1:1 to either the intervention or control arm (Fig. 2). Anonymised data will be collected from eligible patients in both arms at baseline and 1 year post entry into the study. Patients will be informed about being entered into BEST3 data collection by letter. Patients in the intervention arm will receive an invitation for a Cytosponge™-TFF3 test in their general practice. Patients with a positive TFF3 test will receive an invitation for an upper gastro-intestinal (GI) endoscopy at their local hospital-based endoscopy clinic to test for BE. In addition to the TFF3-positive patients, 10% of the patients in each arm (who have not had an endoscopy since the start of the trial) will be randomly selected to be invited for an endoscopy at approximately 12 months.

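### Specificity is defined only among TFF3-negative patients and so equals 100% by construction; the crude sensitivity beside it is inflated by partial verification

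*Protocol article*

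**What the plan says.** Under Statistical analysis, the secondary-endpoints paragraph gives two formulas for diagnostic accuracy in primary care. For sensitivity: "the sensitivity will be calculated as the proportion of TFF3 positive tests in patients with endoscopy confirmed BE (gold standard"). For specificity: "the proportion of TFF3 negative tests in endoscopy confirmed BE negative patients amongst the 10% participants randomly invited to endoscopy from TFF3 negative patients".

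The Design section sets who reaches endoscopy. "Patients with a positive TFF3 test will receive an invitation for an upper gastro-intestinal (GI) endoscopy". Separately, and in addition to them, "10% of the patients in each arm (who have not had an endoscopy since the start of the trial) will be randomly selected" for an endoscopy invitation at about 12 months.

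Table 2 lists different accuracy endpoints for the same objective. PPV is the share of TFF3 positives in whom endoscopy confirms BE. The other is "NPV: proportion of TFF3 negative cases confirmed to not have BE by endoscopy (10% endoscopy"). The Secondary objectives section relies on the same sample: "Inviting 10% of BEST3 participants for a research endoscopy will enable us to assess the diagnostic accuracy". The Economic evaluation section says the model's sensitivity and specificity parameters will be updated to reflect the trial's data.

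**The concern.** Specificity is the share of BE-free patients who test negative, so its denominator must contain the BE-free patients who test positive. The stated denominator cannot contain any. It is drawn from TFF3-negative patients, and the Design section handles TFF3 positives as a separate endoscopy group.

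Sensitivity has the opposite gap. True positives are verified almost completely, while most false negatives never have an endoscopy and so drop out of the denominator.

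Both errors flatter the test. Diagnostic accuracy is a stated secondary objective, and the Discussion says the data are meant to let NICE and other bodies decide on clinical use. In the cost-effectiveness model, a specificity of 100% would remove the cost of endoscopies after false-positive tests, and an inflated sensitivity would hide most missed BE.

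**Working it through.** **Inputs from the protocol.** True sensitivity 85% and BE prevalence 4% (low end of 4–5%), from Sample size calculations. Number tested 2122, same section; the amended plan gives nearly the same, 15,656/2 × 27% ≈ 2114. Share of TFF3 negatives invited at random: 10%, among those without a study endoscopy. Routine endoscopy in false negatives: 10% (Pilot phase and 6-month milestone review). Specificity 92.4% (secondary-care case:control study) or 93.8% (primary-care study), from Table 1.

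**Assumptions.** The protocol gives no expected endoscopy attendance. I use 100%, 50% and 27% for the research endoscopy (27% borrowed from Cytosponge uptake), and 100% or 80% for TFF3 positives.

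**The plan's own figures.** It states no expected sensitivity or specificity estimate. Its sample size does use the same inputs, and these reproduce:
- Original intervention-arm rate: 0.5 × 0.04 × 0.85 + 0.5 × 0.006 = 2.0%. Against 0.6% at 90% power and two-sided 5%, this needs 1514 per arm with continuity correction, as stated.
- Amended rate: 0.27 × 0.04 × 0.85 + 0.73 × 0.006 + 0.27 × 0.15 × 0.006 = 1.38%, which gives the stated 6764 (without continuity correction).

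**Expected counts.** BE: 2122 × 0.04 = 84.9, split into 72.1 true positives and 12.7 false negatives. No BE: 2037.1, split at 92.4% specificity into 1882.3 true negatives and 154.8 false positives (126.3 false positives at 93.8%).

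**Specificity.** With full attendance the 10% sample holds about 188 BE-free patients, all TFF3-negative.
- As written: 188/188 = 100%, for any true value.
- False positives added without weighting: 188/(188 + 155) = 54.9% (60.2% if the truth is 93.8%).
- False positives added and sampled negatives weighted by 10: 1882/(1882 + 155) = 92.4%.

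Both corrections are needed.

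**Sensitivity.** Let f be the fraction of false negatives verified and v the attendance of TFF3 positives. Crude sensitivity = 0.85v/(0.85v + 0.15f). With research-endoscopy attendance u, f = 0.10u if only the random sample counts, and f = 0.10 + 0.90 × 0.10u if routine endoscopy also counts. With v = 1:

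| u | Routine not counted: f, crude sensitivity, false negatives found | Routine counted: f, crude sensitivity, false negatives found |
|---|---|---|
| 100% | 0.100, 98.3%, 1.3 | 0.190, 96.8%, 2.4 |
| 50% | 0.050, 99.1%, 0.6 | 0.145, 97.5%, 1.8 |
| 27% | 0.027, 99.5%, 0.3 | 0.124, 97.9%, 1.6 |

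With v = 80% and u = 100%, the figures are 97.8% (routine not counted) and 96.0% (counted). For other true sensitivities in Table 1 (73.3% to 95.4%), with v = 1, the crude figure runs from about 93.5% to 99.9%.

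**Recovery by a correct method.** Weighted sensitivity: 72.1/(72.1 + 10 × 1.27) = 85.0%. The Table 2 route gives the same. The TFF3-positive proportion is q = (72.1 + 154.8)/2122 = 0.107, with PPV 31.8% and NPV 99.33%.
- Sensitivity = q·PPV/[q·PPV + (1−q)(1−NPV)] = 0.0340/(0.0340 + 0.0060) = 85%.
- Specificity = (1−q)·NPV/[(1−q)·NPV + q(1−PPV)] = 0.887/(0.887 + 0.073) = 92.4%.

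**The case against.** Four points can be made for the plan.

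- *The sensitivity sentence is not confined to the random 10%.* It covers all endoscopy-confirmed BE, and the 12-month data extract captures coded endoscopies and new BE diagnoses. This stands. A reader might infer that sensitivity will read 98–99%. The documents do not support so firm a figure: with the protocol's own 10% routine-endoscopy route counted, it is nearer 96–98%. The upward direction is unchanged.
- *A one-sentence definition does not rule out a verification adjustment in an analysis plan that is not shown.* This is fair for sensitivity, where the lack of weighting is silence. It does not help specificity, where the denominator is stated and wrong.
- *Table 2 still lists PPV and NPV, properly defined, and also the TFF3-positive proportion.* This stands. A reader might infer that the analysis section has replaced those endpoints or that the trial cannot estimate accuracy. Neither follows: nothing withdraws Table 2, and its quantities are enough to recover sensitivity and specificity. The defect is that the analysis section passes over them for two formulas that fail as written.
- *The economic model does not rest on the trial alone.* This stands too. The Economic evaluation section also plans a literature search and value-of-information analyses, so it cannot be said that the model will run on 100% specificity. But it names these two parameters for updating from trial data, so the route for the error is open.

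**Conclusion.** The point holds. Specificity as defined is 100% by construction, with no assumption needed. At Table 1's 92.4–93.8%, it leaves out roughly 126–155 false positives among about 2122 tested.

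Crude sensitivity is biased upward. At a true 85% it would read about 96–99.5%, an excess of some 11 to 14.5 percentage points. That range depends on assumed attendance at both kinds of endoscopy, on whether BE found at routine endoscopy is counted, and on no verification adjustment being applied.

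The error is confined to a secondary objective and what draws on it. The primary comparison, the sample size, the data collected and the Table 2 definitions are untouched.

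**What to change.** In the secondary-endpoints paragraph, make the Table 2 PPV and NPV (by segment length) the accuracy analysis. If sensitivity and specificity are also reported:

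- Include TFF3-positive patients without BE in the specificity denominator.
- Derive both measures from PPV, NPV and the TFF3-positive proportion, or by inverse-probability-of-verification weighting (Begg–Greenes type).
- Use a separate weight for each route to endoscopy: 1/attendance for TFF3 positives; 1/(10% × uptake) for TFF3 negatives verified through the random sample, among those without an earlier study endoscopy; and no 10% factor for TFF3 negatives verified by clinical endoscopy. One common weight for all verified negatives would overcount the last group. The NPV used in the derivation should combine the two negative groups in the same way.
- State the assumption that, within each group, attendance does not depend on BE status.
- Give bootstrap or similar intervals, and pass the corrected values with their uncertainty to the economic model.

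The cost is analysis wording; data collection does not change. The downside is a less favourable and much less precise sensitivity, because only about one or two false negatives are expected to be found. With full attendance and the random route alone, each one found stands for ten. Finding one, two or three would give 72.1/82.1 = 88%, 72.1/92.1 = 78% or 72.1/102.1 = 71%. That imprecision is already in the design; the crude formula only hides it.
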